**Methods:**

Participants are recruited via occupational health services, patient organisations, employers, and a yearly national conference on chronic diseases. They are eligible when they have a chronic physical medical condition, have a paid job, and experience problems at work. Workers on long-term, 100% sick leave that is expected to continue during the training are excluded. After filling in the baseline questionnaire, the participants are randomised to either the control or the intervention group. The control group will receive no care or care as usual. Post-test mail questionnaires will be sent after 4, 8, 12 and 24 months. Primary outcome measures are job retention, self efficacy, fatigue and work pleasure. Secondary outcome measures are work-related problems, sick leave, quality of life, acquired work accommodations, burnout, and several quality of work measures. A process evaluation will be conducted and satisfaction with the training, its components and the training methods will be assessed.

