#### Perceived self-efficacy is a prerequisite to resolving work-related problems

According to social learning theory, active coping behaviour aimed at solving problems will improve when perceived self-efficacy increases [28,29]. Expectations of personal efficacy will be enhanced by performance accomplishments, vicarious experience and verbal persuasion.

The above-mentioned principles resulted in the development of a stepwise intervention for employees with a chronic disease: a) exploring and clarifying work-related problems, b) communication at work, and c) thinking out and realising solutions. It is organised mainly as a group intervention, since group meetings are a suitable method for enhancing perceived self-efficacy.

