## Methods/Design

### Study design, research question, and follow-up

The study is designed as a randomised controlled trial. Eight training groups, with 64 participants in total, will be compared to about 64 persons in the control group. The follow-up is two years, with one baseline questionnaire and four follow-up questionnaires at 4, 8, 12 and 24 months.

The research question is twofold: a) Which work-related problems do employees with a chronic disease experience at the workplace, b) Does participation in the training increase self efficacy, establish work accommodations, decrease fatigue, enhance work pleasure, improve quality of work, and contribute to job retention?

Persons in the control group receive care as usual. However, the usual care for this group of patients for work-related issues varies from nothing at all to counselling or support by occupational health professionals or medical professionals from outpatient clinics.

The Medical Ethics Committee of Academic Medical Center in Amsterdam informally approved of the study idea, but deemed ethical review unnecessary because they perceived no question of 'medical' research.

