### Outcome measures

Primary outcome measures are job retention, self efficacy, fatigue and work pleasure.

Not having a paid job, or having more than six months full-time sick leave in combination with the expectation that return to work is impossible or improbable is considered as job loss.

Self-efficacy is measured by a situation-specific instrument, measuring self-efficacy in solving work and disease related problems. It is developed according to the principles formulated by Bandura [32]. The fourteen items are measured on bipolar five-point Likert scales.

Fatigue is measured with the Checklist Individual Strength (CIS), a well-validated questionnaire for the working population [33]. It has four subscales: fatigue severity (8 items), concentration (5 items), motivation (4 items) and physical activity level (3 items).

Work pleasure is measured with a subscale of the Dutch questionnaire on Perception and Judgement of Work [34].

Secondary outcome measures are work-related problems, sick leave, quality of life, acquired work accommodations, burnout, and three quality of work measures: social relationships with colleagues and supervisor, and worries about work. These are subscales of the Dutch questionnaire on Perception and Judgement of Work [34].

Work-related problems are measured with eight items: having problems with specific work tasks, finishing work, arranging the workplace, commuting, communicating with colleagues, communicating with supervisors, accepting the disease, and balancing work and life at home. The three answer categories are counted as 0 (no), 1 (yes, slightly) or 2 (yes, severely) and are added up to an index measure.

Sick leave is measured as the number of days on sick leave during the last four months.

Quality of life is measured with the validated SF12 [35].

Work accommodations are measured with the Work Accommodations List [9].

Burnout is measured by the Utrecht Burnout Scale (UBOS) [36].

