## Discussion

Vocational rehabilitation interventions for persons with chronic diseases generally focus on entering or re-entering the labour market. Structured vocational rehabilitation interventions aimed at job retention are rare, notwithstanding demands for evidence-based vocational rehabilitation programmes aimed at preventing work disability for this group of employees [38]. Just a few of this kind of interventions could be traced in a systematic review [20]. A reason for this lack of initiatives or lack of documentation and evaluation might be that the societal consequences of work related problems are not felt clearly as long as people are still struggling to retain their jobs. However, when serious problems in work functioning finally result in long-term sickness absence, complete work disability or loss of a paid job, it is difficult to return to work.

The intervention we developed originates from an empowerment perspective and aims to help employees restore the balance of work capacity and work demands. We used a stepwise approach, starting with exploring practical, psychological or social problems, followed by communicating with the supervisor or others at work, and finally developing and implementing solutions.

Most studies on interventions aimed at job retention claim effectiveness. However, these claims are seldom underpinned with a study design offering strong evidence. Studies seldom use pretesting, a control group, a sufficient number of participants or a long-term follow-up. Our study design involves a control group and outcome assessments at five points over two years. We also try to include 128 participants randomised over two conditions.

An inevitable drawback is that participants are not blinded. The research project may trigger the awareness of the problems of participants, which can result in more than usual active coping behaviour in members of the control group.

The results of this study will generate knowledge about the nature of work-related problems and will possibly contribute to better vocational rehabilitation services for employees with chronic diseases. It will put issues at the crossroads of chronic disease and work, and of health care and occupational health on the agenda.

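### Sick leave beyond six months counts as job loss only with an expectation of non-return, so unblinded arms with equal absence could be classified differently on a primary outcome

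*Protocol article*

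**What the plan says.** The *Outcome measures* section of the protocol article lists the primary outcomes: "Primary outcome measures are job retention, self efficacy, fatigue and work pleasure". Job loss has two limbs. One is having no paid job. The other is full-time sick leave beyond six months, which "in combination with the expectation that return to work is impossible or improbable is considered as job loss". The second limb needs both parts, the absence and the expectation. The section does not say who holds the expectation or how it is obtained.

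On data collection, *Study design, research question, and follow-up* gives "one baseline questionnaire and four follow-up questionnaires at 4, 8, 12 and 24 months", and the abstract states that "Post-test mail questionnaires will be sent after 4, 8, 12 and 24 months". No physician rating, blinded assessor or adjudication of job loss is described. The trainer forms under *Process evaluation* concern the sessions, not outcomes.

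The *Discussion* says "An inevitable drawback is that participants are not blinded", and then considers only that controls may cope more actively than usual. It does not consider outcome classification.

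On mechanism, the rationale section on perceived self-efficacy says "Expectations of personal efficacy will be enhanced by performance accomplishments, vicarious experience and verbal persuasion", and explains the choice of format by saying that "group meetings are a suitable method for enhancing perceived self-efficacy".

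**The concern.** Whether someone is at work, and for how long they have been absent, are facts. Whether they are expected to return is a judgement. If that judgement comes from a participant who knows the allocation, and the training makes participants more confident about solving work problems, the judgement can shift without any change in who is working. The training arm would then show fewer counted job losses at equal absence.

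At stake is the reading of a primary outcome that is also one of the two stated aims of the intervention. The expectation clause also brings job retention closer to self-efficacy, which is a separate primary outcome. If greater confidence does lead to return to work, the return itself will show it. The clause gives credit before any return has happened.

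**Working it through.** **The plan's own figures.** The article gives no event rate, effect size or sample-size calculation for job retention. Its one computed figure, 25 per group for fatigue severity, reproduces. The difference in follow-up means is 44.0 − 30.2 = 13.8 with SD 16.8. The normal formula gives 24 per group, and the two-sample t version gives 24.26, rounded up to 25. Nothing in this point depends on it.

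**How classification can diverge.** Take two participants, each with a contract and each on full-time sick leave for more than six months. One expects to return and is not an event. The other thinks return improbable and is an event. Absence and job status are the same, so the expectation alone decides.

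**Illustration of size.** All rates here are assumptions. Both arms have 64 people (the planned size) and identical true status.

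- p_job: proportion with no paid job, 5% or 10%
- p_leave: proportion with a job but on full-time sick leave beyond six months, 5% to 15%
- q: proportion of the latter for whom return is judged impossible or improbable, 70% in controls and either 35% or 50% in trained participants

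The counted job-loss proportion in an arm is p_job + p_leave × q. The spurious hazard ratio is ln(1 − trained) / ln(1 − control). The last column is the approximate chance of a significant result favouring training (normal approximation for two proportions, two-sided 0.05). That chance is 2.5% when q is equal in both arms.

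| p_job | p_leave | q control / trained | Expected events, control vs trained | Hazard ratio | Chance |
|---|---|---|---|---|---|
| 5% | 5% | 70 / 35 | 5.4 vs 4.3 | 0.79 | 5.6% |
| 5% | 15% | 70 / 35 | 9.9 vs 6.6 | 0.64 | 14.1% |
| 10% | 5% | 70 / 35 | 8.6 vs 7.5 | 0.86 | 4.8% |
| 10% | 15% | 70 / 35 | 13.1 vs 9.8 | 0.72 | 11.7% |
| 5% | 15% | 70 / 50 | 9.9 vs 8.0 | 0.79 | 7.0% |
| 10% | 5% | 70 / 50 | 8.6 vs 8.0 | 0.92 | 3.7% |

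Worked example, second row: control 0.05 + 0.15 × 0.70 = 0.155; trained 0.05 + 0.15 × 0.35 = 0.1025; ratio ln(0.8975) / ln(0.845) = 0.1081 / 0.1684 = 0.64.

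**The same scenario without the clause.** Counting all long sick leave gives 64 × (0.05 + 0.15) = 12.8 expected events in each arm and a hazard ratio of 1.0. Counting loss of paid work alone gives 64 × 0.05 = 3.2 in each arm, again 1.0. Either analysis would show that the apparent effect came from the expectation.

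**The case against.** The strongest objection is that the article does not name the rater. It condenses a fuller document, which may specify one. A reader might infer that the expectation can only come from the participant, but the article does not say so. Self-report is the likelier reading, because participant questionnaires are the only source described. A rating by someone unaware of allocation would largely remove the concern. This part of the objection stands.

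A reader might also infer that the training is designed to change the belief about return to work. No section names that belief as a target. The self-efficacy measure concerns solving work and disease related problems, and the description of session 2 says thoughts and feelings are to be understood rather than replaced. The link is an inference from a related construct.

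Nor is it established that the bias must favour training. The programme covers disability legislation and asks for realistic plans, so trained participants could become more sober about return. Swapping the 70% and 50% between arms turns the two ratios above into 0.1684 / 0.1335 = 1.26 and 0.1450 / 0.1335 = 1.09.

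A reader who looks only at the sick-leave limb might speak of job loss being halved. With an assumed 6 long absences per arm, 4 counted against 2 gives a ratio of 0.5, but that leaves out the unaffected limb. Adding 3.2 people without a job to each arm gives 7.2 against 5.2, a ratio of 0.72; adding 6.4 gives 10.4 against 8.4, or 0.81. The limb may also be small, since workers on long-term full sick leave expected to continue are excluded at entry.

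Finally, the clause has a reason. Someone with a contract who is expected back has not lost the job, so making absence alone the primary definition would turn a retention outcome into an absence outcome. This argues against replacing the definition, but not against a sensitivity analysis. The sick-leave measure described, days in the last four months, cannot by itself establish a spell beyond six months. The job-loss definition, however, already requires that status to be known.

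**Conclusion.** The point holds in a limited form. One limb of one of four primary outcomes depends on an expectation whose source is not stated. The only outcome source described is unblinded participants, and the training aims to raise related expectations. Classification could therefore differ between arms at equal absence, probably but not certainly in favour of training. The limb for having no paid job is not affected.

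The size cannot be derived from the documents. Under the assumed rates, the spurious hazard ratio is about 0.64 to 0.86 when 70% of controls and 35% of trained participants on long leave are judged unlikely to return, and about 0.79 to 0.92 with 70% against 50%. The chance of a false significant result in favour of training rises from 2.5% to about 5–14% and 4–7% respectively. These figures assume identical true status in both arms and rest on a normal approximation with few events, so they show the order of magnitude only. With so few events, reclassifying two or three people can change the conclusion, which is enough to justify a cheap safeguard.

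**What to change.** Keep the current definition as primary. Pre-specify two sensitivity survival analyses of job retention: one counting all full-time sick leave beyond six months as an event whatever the expectation, and one counting only loss of paid work. Claim a job-retention effect only if these agree with the primary analysis in direction and approximate size. Significance should not be required of them, because the second in particular will have few events.

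State whose expectation is used. Where a source already exists that does not depend on the participant's knowledge of allocation, take the expectation from there.

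The cost is a short addition to the outcome and analysis text and one or two extra analyses, using an absence status that the definition already requires. The downside is that the first sensitivity analysis counts some people who later return to work as events, under the same rule in both arms.

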### Sample size and power

The sample size is based on detecting a difference in fatigue, measured with the fatigue severity subscale of the Checklist Individual Strength (CIS). Power calculations have been made with an alpha of 0.05 and a power of 80%. Studies examining the effect of interventions on fatigue of persons with a chronic disease are rare. Stulemeijer et al (2005) studied the effect of cognitive behaviour therapy for adolescents with chronic fatigue syndrome in a randomized controlled trial. In the treatment group fatigue severity decreased from 52.5 to 30.2 (sd = 16.8), compared to a decrease from 51.6 to 44.0 for the control group [37]. Based on these figures, we need 25 persons in the intervention group and the control group each.

Our intervention resembles Stulemeijer's intervention in its aim to decrease fatigue. However, whereas Stulemeijer's intervention focused on the disease and its symptoms, our empowerment training for employees focuses on work related problems and resulting work stress and fatigue. The chronic disease itself will remain and might even progress, which means that fatigue levels comparable with those of the healthy workforce are not to be expected at follow-up. This is the reason why we have chosen a larger sample, of 64 persons in the intervention group and the control group each.

### Statistical analysis

Statistical analyses will be performed according to the intention-to-treat principle. Job retention will be analysed using survival analysis. The other variables will be analysed with repeated measurement analysis and mixed linear models.

### Process evaluation

The process of the intervention will be evaluated in three ways. First, we will describe the recruitment of participants and evaluate if we reached the target group and if our recruitment methods worked or failed. The researcher keeps a recruitment diary for this purpose. Second, the group sessions and the individual sessions will be evaluated by the trainers. They fill in a process evaluation form and note the attendance of the participants, whether each subject for that session has been discussed, whether the participants experience emotional or cognitive difficulties with the subject, whether they feel involved, and whether the goal of the specific subject is reached. Third, the participants are asked their opinion in the post-test questionnaires. They are asked to evaluate the whole training, the various themes and procedures, and the textbook. They are also asked to evaluate whether skills they wanted to improve have actually improved, whether they have passed successfully through the three stages: clarification, communication and problem solution, and whether they have attained the goal they had in mind beforehand.

## Discussion

Vocational rehabilitation interventions for persons with chronic diseases generally focus on entering or re-entering the labour market. Structured vocational rehabilitation interventions aimed at job retention are rare, notwithstanding demands for evidence-based vocational rehabilitation programmes aimed at preventing work disability for this group of employees [38]. Just a few of this kind of interventions could be traced in a systematic review [20]. A reason for this lack of initiatives or lack of documentation and evaluation might be that the societal consequences of work related problems are not felt clearly as long as people are still struggling to retain their jobs. However, when serious problems in work functioning finally result in long-term sickness absence, complete work disability or loss of a paid job, it is difficult to return to work.

The intervention we developed originates from an empowerment perspective and aims to help employees restore the balance of work capacity and work demands. We used a stepwise approach, starting with exploring practical, psychological or social problems, followed by communicating with the supervisor or others at work, and finally developing and implementing solutions.

Most studies on interventions aimed at job retention claim effectiveness. However, these claims are seldom underpinned with a study design offering strong evidence. Studies seldom use pretesting, a control group, a sufficient number of participants or a long-term follow-up. Our study design involves a control group and outcome assessments at five points over two years. We also try to include 128 participants randomised over two conditions.

An inevitable drawback is that participants are not blinded. The research project may trigger the awareness of the problems of participants, which can result in more than usual active coping behaviour in members of the control group.

The results of this study will generate knowledge about the nature of work-related problems and will possibly contribute to better vocational rehabilitation services for employees with chronic diseases. It will put issues at the crossroads of chronic disease and work, and of health care and occupational health on the agenda.
